**Figure 2: Identification of patients to approach for study participation**

[figure not shown]

## **Consent**

The consent process will seek permission for the use of routinely recorded healthcare data and for one study-specific assessment:

- Routinely recorded information from ambulance and hospital healthcare records will include: demographic details, stroke symptoms, physiological observations, relevant medical history and medications, CT scan result, thrombolysis assessment, thrombolysis outcome on day 2 (if relevant) and health status at discharge. In NHS stroke services these data items are systematically recorded for individual patients in healthcare records and reported publically at service level as a requirement of the mandatory prospective audit funded by the Department of Health i.e. the Sentinel Stroke National Audit Programme (SSNAP).
- The study-specific assessment will include collection of health outcome and resource utilisation information at 90 days after stroke. This will be conducted by face to face interview, telephone interview or postal questionnaire.

### **Consent for patients who can be approached about study participation during their inpatient stay**

#### ***i. Consent for patients with mental capacity***

For eligible patients with capacity to consent to research, a trained member of the clinical team or NHS research support staff will approach the patient to discuss the study and provide a patient information sheet. After allowing sufficient time for potential participants to decide whether to take part in the study and an opportunity to ask questions, consent will be obtained in writing.

When a patient has mental capacity but is unable to sign the consent form (e.g. because of weakness of the dominant hand following stroke), consent will be confirmed orally in the presence of a witness (an individual not otherwise involved in the trial) and the witness will sign and date the consent form on behalf of the participant.

#### ***ii. Consent for patients with mild communication difficulties***

For patients with mild communication difficulties due to the effects of stroke upon the use and understanding of language (aphasia), a set of 'easy access' study documentation will be used. After allowing sufficient time for the information (including an 'easy access' patient information sheet) to be considered and an opportunity to ask questions, consent will be obtained in writing using the 'easy access' consent form. NHS research support staff working within stroke services are experienced in communicating with patients with aphasia but specialist advice can be sought from the local stroke speech and language therapy service if required.

#### ***iii. Consent for patients who lack mental capacity***

It is anticipated that approximately one third of study eligible patients will be unable to engage with an informed consent process due to the effects of stroke upon communication and cognition. As exclusion of this group would drastically reduce the clinical relevance of the study, if a patient has been identified as eligible but is unable to provide consent, a personal or professional consultee will be approached as detailed below..

For potential participants who lack capacity to consent to research, a trained member of the clinical team or NHS research support staff will attempt to identify an appropriate personal consultee (usually the next of kin) to approach, discuss the study and provide a consultee information sheet. If a personal consultee is identified, after allowing sufficient time for him/her to consider the patient's wishes and feelings and an opportunity to ask questions, the consultee will be asked to complete a consultee declaration form if they believe the patient would have no objection to taking part in the study.

In the event of being unable to locate an appropriate personal consultee, an independent clinician (professional consultee) will be asked to confirm that the patient lacks capacity for consent, and that study participation would not introduce a risk of harm or be against the patient's wishes from what is known about their character and beliefs. The independent clinician will sign an independent clinician declaration form concerning study participation.

As it is likely that the communication or cognitive difficulties that impeded a patient's ability to provide consent will still be present at 90 days after stroke, where a personal consultee provided permission to enter the study, this person will be contacted to answer the 90 day health outcome questions on behalf of the patient. In cases where an independent clinician provided permission for study participation, only routinely available data will be collected at 90 days. The participant will not be contacted.

#### **iv. *Consent and early mortality***

The early mortality rate following acute stroke is approximately 10%. These patients are usually identified on admission and treated palliatively. However, unexpected deaths also occur. Exclusion of patients that die soon after admission would reduce the study's relevance for the typical clinical stroke population.

When a patient has died or if a formal palliative end of life care process has been started at the point when the patient is identified as eligible for the study, individual patient consent will not be possible and it is likely to be distressing for a personal consultee to be approached regarding the research use of routinely collected healthcare data. The 90 day health outcome will not be relevant. Under these circumstances the local PI will sign an Early Mortality / Palliative Care Declaration Form to confirm that the patient has died or is in a formal palliative phase, and take responsibility for the use of routinely collected healthcare data for this research project.

Acute stroke has many effects upon neurological function and consciousness which can fluctuate for several days or even weeks. There may be unusual instances where a patient who has been entered into the study using this Early Mortality/Palliative Care Declaration form subsequently shows enough signs of improvement that supportive care is re-instated, and may still be alive at day 90. However, these are likely to be challenging clinical situations where seeking an alternative method of consent will be difficult because of the severe degree of remaining neurological impairment and time elapsed since admission. In these unusual scenarios, an alternative method of consent will not be pursued and the day 90 study specific assessment will not be conducted. Routinely available data collected as part of standard clinical care will be retained as per the original PI declaration and used in the analysis.

#### **v. *Loss of capacity to consent to research during participation in the study***

When participants have provided their own consent to take part in this research project, it is possible that they may temporarily (e.g. because of intercurrent illness) or permanently (e.g. because of further stroke) lose the capacity to assist with the 90 day outcome assessment. On entering the study, participants will be asked to nominate a personal consultee (relative or close friend) who may be contacted to answer the 90 day health outcome questions on their behalf, should they be unable to undertake this assessment personally.

#### ***Consent for patients who are only identified as study eligible after discharge from hospital***

Patients who have only been identified as study eligible after hospital discharge will receive an invitation letter, patient information sheet, consent form and pre-paid return envelope by post. Patients willing to take part in the study will be asked to return a completed consent form. Invited patients who have not returned a consent form within four weeks will receive one phone call from the local hospital research team. Thereafter, patients will only be further contacted about the study if a consent form is returned,

Figure 3 summarises the decision process for obtaining study consent,

### ***Consent forms***

Original consent forms will be retained in the investigator site file at each study site. A copy of the form will be filed in the medical records, with a further copy given to the participant. For participants returning the consent form by post, a copy of this will be returned to the participant along with a letter acknowledging receipt and study participation.

The information sheets and consent forms will be available in English. However, interpreters and translation of written material will be possible through local NHS arrangements should potentially eligible patients require this.

**Figure 3. Decision process for study consent**

[figure not shown]

*\*When a patient has mental capacity but is unable to sign the consent form (e.g. because of weakness of the dominant hand following stroke), consent may be confirmed orally in the presence of a witness (an individual not otherwise involved in the trial) using the box at the bottom of the standard consent form.*

### 13. Study data collection

Data for this study will be collected day 1 pre-admission, day 1 post-admission, day 2 (if thrombolysis administered) and 90 days (+/- 7 days) post stroke.

#### Day 1 pre-admission data:

Suspected stroke diagnosis (FAST; paramedic judgement of stroke or query stroke)  
Symptom onset or last known to be well time (paramedic judgement)  
Pre-notification of receiving hospital  
Times of 999 call, ambulance on scene, ambulance left scene and hospital arrival  
Involvement of rapid response paramedic: yes/no (intervention group only)  
Time of transfer of care (also called handover) from the paramedic to the hospital team  
Time of paramedic signature of the completed ambulance clinical record  
Time paramedic is clear to respond to another incident

The above data will predominantly be transcribed from the routine ambulance clinical record onto a study specific Case Record Form (CRF) by NHS research support staff or other hospital clinical staff trained to deliver this research project. However, some data items are not contained within the routine ambulance clinical record but held within computerised ambulance service dispatch systems. These data will be obtained directly from the ambulance services. For participants travelling to hospital with an intervention paramedic trained to deliver the PASTA pathway, some of the above data will also be recorded onto a study specific paramedic CRF which will additionally record delivery of the PASTA pathway.

#### Day 1 post-admission data:

Demographic information (age; gender; pre-stroke mRS)  
Date/time of hospital admission  
First blood pressure reading on admission  
First blood glucose reading on admission (capillary or serum glucose)  
Stroke severity on admission (National Institute of Health Stroke Score)  
Stroke onset or last known to be well time (stroke team judgement)  
Current use of anticoagulant medication  
Previous medical history (stroke; TIA; heart failure; atrial fibrillation; diabetes; hypertension)  
Hospital admission locations (ED; stroke unit; critical care; medical admissions ward, other ward)  
First brain imaging time, modality and result (CT / MRI; infarction/primary intracerebral haemorrhage)  
Thrombolysis treatment decision (yes / no; reason why thrombolysis not administered)  
Date/time of thrombolysis (if received)  
Use of other treatments (reversal of anticoagulation if haemorrhagic stroke; acute blood pressure lowering if haemorrhagic stroke or before intravenous thrombolysis; referral or transfer to neurosurgery; referral or transfer for intra-arterial treatment; use of intra-arterial treatments (yes / no; time of puncture)).  
Entry into another clinical trial on day 1 after admission (yes / no; which one)  
Date and time of admission to first stroke unit  
Date and time of assessment of swallow safety at first hospital

#### Day 2 thrombolysis outcome (if administered):

Stroke severity (NIHSS) at 24-48 hours after thrombolysis treatment (and/or intra-arterial treatment if received): standard post thrombolysis stroke severity measurement.  
Complications (symptomatic intracranial haemorrhage / extracranial bleed / angioedema / other complication) within 48 hours of thrombolysis treatment (and/or intra-arterial treatment if received): standard post thrombolysis complications measurement.

The post admission data are all routinely collected clinical data. They will be transcribed from routine medical records onto a study specific hospital CRF. This will be performed by NHS research support staff or other clinical staff trained to deliver this research project.

**Day 90 (+/- 7 days) data:**

At day 90, both data related to hospital discharge from this continuous inpatient episode and health at 90 days after stroke will be collected.

*Data related to discharge due to completion of all inpatient care:*

Died during this inpatient episode for stroke (yes/no)  
Cause of death  
Date of death (if relevant)  
Discharge date or record that the patient is still an inpatient at day 90 (yes/no)  
If still an inpatient at day 90, has there been stroke recurrence  
Discharge destination at completion of this inpatient episode (own home, different private address (eg relative) care home, other)  
If discharged to a care home, was the patient previously resident / not previously resident  
Rehabilitation arranged at discharge (none, early supported discharge team, community rehabilitation team, both)  
Assistance with activities of daily living required at discharge (yes/no; if yes: what support received: informal carers/paid carers/both)  
If paid carers then how many visits per week provided at discharge  
Dependency at discharge (mRS)

*Data related to day 90 health:*

Died after stroke event discharge but prior to 90 days (yes/no)  
Date of death (if relevant)  
Cause of death (if available)  
Readmission(s) to hospital since discharge; reason for admission(s), length of stay(s).  
Readmission was due to stroke recurrence (yes, no)  
Current (90 day) residence (hospital, home, different private address, care home, other).  
Current (90 day) dependency (simplified questionnaire mRS[25])  
Community rehabilitation since discharge (therapy received (yes/no); received at home/hospital/both; number of weeks received; less than, equal to or great than one appointment/week).  
Current (90 day) assistance with activities of daily living (yes / no; if yes: what support received: informal carers/paid carers (how many visits per week) /both)

For all participants, confirmation that stroke remains the diagnosis assigned for the event where consent was obtained. If not, the new diagnosis assigned.

Day 90 data consists of both routinely collected clinical data and study specific data. Routinely collected clinical data will be transcribed from routine medical records onto a study specific CRF. Study specific data will be collected by face to face interview, telephone interview or by postal questionnaire. Telephone interview with the participant or consultee will be the main method, undertaken by NHS research support staff.

In instances where a participant/personal consultee cannot be contacted by telephone after one week of attempting to locate him/her, a postal questionnaire will be used. A postal questionnaire will also be used where telephone interview is not be possible (e.g. participant does not have a telephone). A single postal questionnaire with enclosed reply-paid envelope will be mailed. It will also be possible to collect 90 day study specific data by face to face interview conducted by NHS research support staff. This option will be used at the discretion of staff but predominantly when participants are currently hospital inpatients.

Where it has not been possible to obtain the 90 day study specific data by 6 months after stroke, NHS research support staff will use the routine hospital data administration systems to re-confirm whether the participant was alive or dead at 90 days. This is necessary because deaths in the community can take some time to appear in the routine hospital records. The mRS (primary outcome measure) is scored 6 for death[26].

All study data will be entered locally onto a secure online database maintained by Newcastle Clinical Trials Unit. Pseudo-anonymised participant identification codes will be used. Study paper CRF's will be kept securely in the local investigator site file.

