### **Expected adverse events**

The PASTA pathway is embedded into standard clinical practice for a clearly defined time interval, during which patients will be closely supervised by qualified ambulance and hospital professionals. Deterioration in the health status of stroke patients commonly occurs in clinical practice: average inpatient mortality is 17% in NHS services[5]; 2% patients treated with thrombolysis deteriorate due to the recognised side effect of cerebral haemorrhage[6]; the stroke recurrence rate is up to 6% within the first 3 months[27]. The following are therefore expected adverse events:

Death directly due to the initial stroke.  
Thrombolysis related cerebral haemorrhage.  
Stroke recurrence leading to new hospitalisation.

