### **Recording and reporting of adverse events**

This study will only report adverse events which are considered to be serious.

In addition, apart from death, adverse events which are considered to be serious will only be reported up until seven days after study entry (ie for one week after the date of the paramedic assessment).

After seven days, there is no possible mechanism by which the study intervention can cause new adverse events. This approach mirrors other clinical trials of emergency stroke treatment where the longer term risk of unforeseen adverse events from the study intervention is very low. Any adverse events that do occur will be in the immediate peri-admission period as the intervention has been designed to facilitate the emergency administration of intravenous thrombolysis to appropriate stroke patients. Thrombolysis treatment is widely used in clinical practice and its adverse events are already well described. It can only be given once within 4.5 hours of stroke onset and has lost all pharmacological action within 24 hours. The study intervention does not change the clinical criteria for thrombolysis administration. Therefore it is not possible for any adverse events after the emergency phase to be attributed to the study intervention. To provide additional reassurance, the reporting period has been set at 7 days rather than just 24 hours.

Deaths will be recorded for the duration of a participants involvement in the study (until 90 days after stroke).

Serious Adverse Events will also **exclude**:

- The expected adverse events listed above (these will be routinely recorded and monitored as part of study data collection)
- Pre-planned hospitalisations and scheduled treatment for pre-existing conditions.

A study SAE form will be completed for all SAEs. To ensure complete capture of SAE's, the 90 day study CRF will include a question to ask staff to check for medical events that fulfil the criteria to be a SAE. For any events which fulfil the above criteria to be a SAE and are unreported, the study SAE form will be completed.

Serious adverse events, regardless of causality or expectedness, will be reported to the Chief Investigator. SAEs will also be reported to the trial sponsor (Newcastle Upon Tyne

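### A non-fatal stroke recurrence in hospital from day 8 onward is not recorded for patients discharged before day 90, so recurrence counts depend on discharge date

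*Protocol*

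**What the plan says.** Section 13 of the protocol (Day 90 data) contains two recurrence items. Among the items on the index admission: "If still an inpatient at day 90, has there been stroke recurrence". Among the items on health at day 90, attached to readmissions since discharge: "Readmission was due to stroke recurrence (yes, no". The day 1 and day 2 data lists in the same section have no recurrence item.

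Section 17 (Recording and reporting of adverse events) sets the SAE window: "apart from death, adverse events which are considered to be serious will only be reported up until seven days after study entry". The day 90 form prompts staff to look for missed SAEs, but within the same limits: "For any events which fulfil the above criteria to be a SAE and are unreported, the study SAE form will be completed".

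Section 17 also exempts the listed expected events from SAE reporting because they are tracked through study data. The one that concerns recurrence is "Stroke recurrence leading to new hospitalisation". As background it states that "the stroke recurrence rate is up to 6% within the first 3 months".

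**The concern.** Whether a recurrence during the index admission is recorded depends on when the patient goes home. Take two patients with the same non-fatal recurrence in hospital on day 30. If one is discharged on day 89 and the other is still an inpatient at day 90, the first event has no field and the second is recorded. The protocol gives no reason for the condition, and the neighbouring items on the index admission (death, destination, dependency) are not limited to patients still in hospital.

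Any count of recurrence drawn from these data would be incomplete to a degree that varies with length of stay. Section 10.2 lists stroke recurrence itself among the complications that influence length of stay, so coverage is not independent of the event being counted. An analysis plan cannot repair this, because the event is never collected.

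**Working it through.** **Coverage by route, for a non-fatal recurrence**

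| When and where | Route | Recorded? |
|---|---|---|
| Up to day 7, in hospital | SAE form, if judged serious (not an excluded event) | Yes |
| Day 8 to discharge, discharged before day 90 | SAE window closed; not a readmission; index-stay item not asked | No |
| Day 8 to day 90, still an inpatient at day 90 | Index-stay item | Yes |
| After discharge, readmitted | Readmission item | Yes |
| After discharge, not readmitted | None after day 7 | No |

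The day 90 SAE check does not close the second row, because it applies only to events that already meet the SAE criteria, including the seven-day limit. A fatal recurrence is visible in any row, because deaths and their causes are collected to day 90.

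**Length of the gap.** Let L be length of stay in days. If L < 90, gap = max(0, L − 7). If L ≥ 90, gap = 0. For L = 30: 30 − 7 = 23 days, and 23/90 = 26% of the follow-up period.

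**Illustration of the effect on a recorded rate.** The protocol states no recurrence rate for this trial to reproduce. I take its background figure of 6% at 90 days as the true risk at every L. I assume that all recurrences up to day 7 reach an SAE form, that all recurrences after discharge lead to readmission, and that none is fatal. Recorded rate = 6% − [F(L) − F(7)] for 7 < L < 90, under two assumed time courses:

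- Constant hazard: λ = −ln(0.94)/90 = 0.000688 per day, F(t) = 1 − exp(−λt). For L = 30: 2.04% − 0.48% = 1.56% missed, so 4.44% recorded.
- Front-loaded hazard (Weibull, shape 0.5): F(t) = 1 − exp(−0.0619·√(t/90)). For L = 30: 3.51% − 1.71% = 1.80% missed, so 4.20% recorded.

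| L (days) | Gap (days) | Share of 90 days | Recorded, constant | Recorded, front-loaded |
|---|---|---|---|---|
| ≤ 7 | 0 | 0% | 6.00% | 6.00% |
| 14 | 7 | 8% | 5.52% | 5.30% |
| 21 | 14 | 16% | 5.05% | 4.77% |
| 30 | 23 | 26% | 4.44% | 4.20% |
| 60 | 53 | 59% | 2.44% | 2.78% |
| 89 | 82 | 91% | 0.54% | 1.74% |
| ≥ 90 | 0 | 0% | 6.00% | 6.00% |

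True risk is the same in every row; only the recording changes. If the index-stay item were asked of everyone, the last two columns would read 6.00% throughout.

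**Effect on a comparison between arms.** At an even spread of 6%/90 = 0.067 percentage points per day, an assumed two-day difference in stay, within the range where the gap applies, shifts the recorded rate by about 0.13 points. On the planned 432 intervention participants that is 0.0013 × 432 ≈ 0.6 of an event.

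**The case against.** The strongest reply is that nothing the protocol commits to is broken. Recurrence is not a primary or secondary outcome (sections 4 and 6.2), and section 18 plans no analysis of it by name. The expected event that section 17 undertakes to track is recurrence leading to a new hospitalisation, and the readmission item captures exactly that. The seven-day limit is deliberate and argued: section 17 holds that later events cannot be attributed to the pathway. The worst consequences still surface, fatal recurrence through cause of death and disabling recurrence, unattributed, through the modified Rankin score. The large gaps in the table belong to very long stays, and no length-of-stay distribution shows how common those are.

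All of this stands, and it keeps the point small. It does not explain the condition. The argument about attribution supports a short SAE window, but not asking the index-stay question of some patients and not of others.

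A reader might go further and infer any of the following, which the protocol does not support:

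- That the trial fails a planned comparison with 6%. That figure is background explaining why some events are expected; no comparison is planned.
- That the data monitoring committee is shown an undercount. Section 24 says only that it has access to unblinded outcome data, not that it receives recurrence rates.
- That the gap falls where risk is highest. Section 10.2 links severity to length of stay, but no passage links either to a higher risk of recurrence.
- That the arms are biased by construction. Bias needs a difference in length of stay between arms, and none is documented.

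**Conclusion.** The gap is real and follows from the text alone: a non-fatal recurrence in hospital from day 8 to discharge, in a patient discharged before day 90, is not recorded. The uncovered window is max(0, L − 7) days. It grows with length of stay and closes for patients still in hospital at day 90. Descriptive or safety counts of recurrence therefore depend on discharge date.

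The primary outcome, the listed secondary outcomes and the sample size are untouched. How many events would be missed cannot be stated. The recorded rates in the table rest on assumed hazard shapes, on the protocol's upper background figure of 6%, and on length of stay being treated as fixed. On the same assumptions, a modest difference in stay between arms shifts the comparison by less than one event. This is a cheap improvement to data collection, not a threat to the trial's conclusions.

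**What to change.** Remove the condition from the index-admission item in section 13 and ask it of every participant's record, for example: *Stroke recurrence during this inpatient episode (yes/no; date)*. Keep the readmission item as it is. Describe any figure reported by arm as recurrence in hospital or leading to readmission by day 90, not as all recurrence, because a recurrence after discharge without readmission would still go unrecorded.

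The cost is one changed form item and slightly more record review at day 90, when discharge data are already taken from the medical records. Participants who have completed follow-up could be back-filled from records, provided the consent described in section 12 for use of routinely recorded data is confirmed to cover this item.
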